# Efficacy and safety of *Ojeok-san* in Korean female patients with cold hypersensitivity in the hands and feet: study protocol for a randomized, double-blinded, placebo-controlled, multicenter pilot study

**DOI:** 10.1186/s13063-018-3013-9

**Published:** 2018-11-29

**Keywords:** Herbal medicine, Cold temperature, Cold hypersensitivity, Randomized clinical trial, Korean medicine

## Abstract

**Background:**

This study aims to evaluate the safety, efficacy, and feasibility of a full randomized clinical trial of *Ojeok-san* in Korean female patients with cold hypersensitivity in the hands and feet.

**Methods:**

This study is a multicenter, double-blinded, randomized, placebo-controlled, two-arm, parallel-group pilot clinical trial. A total of 60 participants will be enrolled and randomly assigned to the *Ojeok-san* treatment group or the placebo control group, in a 1:1 ratio using an Internet-based randomization system. Each group will be administered *Ojeok-san* or placebo three times per day for 8 weeks. The primary outcome will be the mean change in the Visual Analog Scale scores of cold hypersensitivity in the hands from baseline to week 8. Secondary outcomes will include the mean changes in the skin temperature of the extremities, recovery rate of the skin temperature of hands after cold stress test, and the score of Korean version of the WHO Quality of Life Scale abbreviated version.

**Discussion:**

The findings of this study should provide meaningful information for a further large-scale, randomized controlled trial to confirm the safety and efficacy of *Ojeok-san* on cold hypersensitivity in the hands and feet in female patients.

**Trial registration:**

ClinicalTrials.gov, ID: NCT03083522. Registered on 20 March 2017.

**Electronic supplementary material:**

The online version of this article (10.1186/s13063-018-3013-9) contains supplementary material, which is available to authorized users.

## Background

Cold hypersensitivity in the hands and feet (CHHF) is a common complaint in female patients in East Asian countries. It is defined as a subjective symptom in which the individual feels strong coldness in the extremities compared with other individuals under any environmental conditions [1, 2]. According to the Comprehensive Survey of Living Conditions 2013, 32.6% of Japanese women have a complaint of CHHF compare to 15.3% of men [3]. The prevalence of CHHF in Korea has been reported as approximately 12%, with greater effect on the quality of life in the Korean female as compared to the Korean male population [4].

In Korea, the general structure of the healthcare system is pluralistic, providing conventional and traditional Korean medicine based on the patient’s choice. It has the advantage of offering a broad range of medical support to patients based on their own decision [5]. However, due to the lack of evidence on the etiology of CHHF, the standardized clinical practice guideline on CHHF is not yet fully developed, and may provide less certainty and positive expectations of improvement to patients.

Currently, the conventional medicine (CM) perspective on the mechanism of CHHF includes the reduction of peripheral blood flow in the extremities or the increase in peripheral vasoconstriction during exposure to cold temperatures such as, Raynaud’s phenomenon (RP). The common treatment plans of RP consider alleviating each accompanying symptoms itself, including vasodilators, calcium-channel blockers, and lifestyle modifications, but the therapeutic effects of such treatments are debatable [6, 7].

However, traditional Korean medicine (TKM) offers a different perspective on CHHF from ancient times. Based on the diagnostics of TKM, CHHF has been classified as a cold-related symptom as well as a cold syndrome, which requires careful attention to prevent symptom aggravation and further pattern progression into a severe condition [8]. This syndrome is generally categorized into three types by different pathogens. The first type is the invasion of external pathogen of cold through the mouth or body surface, and affects the whole-body condition. The second type is the disharmony of specific internal organs, such as spleen *yang* deficiency, kidney *yang* deficiency, blood deficiency, or *Qi* deficiency. The third type is simultaneous occurrence of cold and heat syndrome due to loss of stomach harmony and lowering adverse *Qi* [1, 9].

The traditional herbal formula, *Ojeok-san* (OJS; *Wuji-san* in Chinese, *Goshaku-san* in Japanese) has originated from the traditional Chinese medicine (TCM) classic *Prescriptions from the Great Peace Imperial Grace Pharmacy* by Chen Shiwen [10]. OJS is known as a general prescription that treats pathogen accumulation due to internal and external invasion by pathogenic factors, such as cold, *Qi*, blood, phlegm, and food. Based on the TKM literature review on OJS, the main indications of OJS are pain in various body parts, gynecological and gastrointestinal symptoms, such as whole-body pain, back pain, CHHF, vomiting, and diarrhea [11–13]. OJS has been widely used in traditional herbal prescriptions, accounting for approximately 30% of drug utilization among the list of National Health Insurance (NHI)-covered herbal preparations in 2011 in Korea [14]. The TKM expert survey on the epidemiology and treatment of CHHF also has indicated that OJS was one of the frequently prescribed medication for CHHF treatment in the clinical field [1, 2].

Despite evidence from TCM and TKM literature and clinical consensus on OJS as a CHHF treatment, a clinical trial to assess the efficacy and safety of OJS has not yet been conducted in any East Asian population. Thus, a well-designed, high-quality, multicenter, randomized, double-blinded, placebo-controlled trial is needed to provide more evidence for the treatment of patients with CHHF using herbal medicine.

## Methods

### Objective

We will evaluate the feasibility of a full randomized clinical trial (RCT) of OJS on Korean female patients with CHHF to evaluate CHHF symptom reduction after 8 weeks of OJS medication as compared with the placebo group.

### Trial design and setting

This trial is a randomized, double-blinded, parallel-group, placebo-controlled, multicenter, pilot study that will be conducted at the following sites: Semyung University second affiliated Oriental Medical Hospital at Chungju, Kyung Hee University Oriental Medical Center, and Kyung Hee University Oriental Medicine Hospital at Gangdong. The total duration of study period is approximately 13 weeks from the screening visit (Fig. 1). The protocol design is based on the Consolidated Standards of Reporting Trials (CONSORT) guidelines and Standard Protocol Items: Recommendations for Interventional Trials (SPIRIT) Checklist (see Additional file 1).

**Fig. 1 Fig1:**
[figure not shown]
Flow chart of study procedure

A total of 60 participants, who voluntarily confirm their willingness to participate in this trial, will be recruited. Written informed consent will be obtained after giving sufficient explanation and period of time for thoughtful decision. Once the participant agrees to participate in this trial, they will be asked to undergo several medical checkups for identifying ineligible participants. After 1 week of run-in period, qualified eligible participants will be randomly assigned to the OJS or the placebo group. They will be administered the investigational products (IP) for 8 weeks and one follow-up visit will be scheduled at 4 weeks after discontinuation of medication (Table 1). The participants will be asked to return any unused investigational drugs at every visit to monitor adherence in order to calculate compliance. During the trial, the participants will be prohibited from receiving other weight-loss treatment.

**Table 1 Tab1:** The detailed trial schedule

		Study period				
		Screening	Treatment period			Follow-up period
Visit		visit 1 (D − 7~ − 2)	visit 2 (D 1)	visit 3 (D 28)	visit 4 (D 56)	FU1 (D 84)
Informed consent		●				
Eligibility assessment		●				
Random allocation			●			
Socio-demographic investigation^a^		●				
Medical and drug history^b^		●				
IP distribution	OJS		●	●		
	Placebo		●	●		
Assessment						
General physical examination		●	●	●	●	●
Severity of CHHF (VAS)		●	●	●	●	●
Skin temperature measurement^c^		●	●	●	●	●
Quality of life (WHOQOL-BREF)			●	●	●	●
Cold stress test			●		●	
Vital signs		●	●	●	●	●
*Anthropometric variables*		●	●	●	●	
Chest x-ray and EKG		●				
Clinical pathological laboratory test		●			●	
Medical and drug history check-up			●	●	●	●
Adverse event check-up				●	●	●
Compliance check-up				●	●	
Blind assessment					●	

^a^Sex, date of birth, age, level of education, occupation, marital status, diet, exercise, smoking, drinking, sleeping condition, motivation of participation, etc.

^b^Including medical and drug history of CHHF

^c^Skin temperature of palm (PC9) and anterior upper arm (LU4) will be measured at the screening visit; skin temperature of thigh (ST32) and instep of foot (LR3) will also be collected additionally at visit 2

Abbreviations: *CHHF* cold hypersensitivity in the hands and feet, *EKG* electrocardiogram, *IP* investigational products, *OJS ojeok-san*, *VAS* Visual Analog Scale, *WHOQOL-BREF* WHO Quality of Life abbreviated version

### Randomization

An independent professional statistician from the contract research organization (CRO), the Institute of Safety, Efficacy, and Effectiveness Evaluation for Korean Medicine (ISEE), will be created with a block size of 2 or 4 and hospital stratification by using SAS (version 6.1.; SAS Institute Inc., Cary, NC, USA). The ISEE also develops and controls the web-based randomization system with an allocation ratio of 1:1. Randomization number assignment via the web-based system will be performed at visit 2 by site the clinical research coordinator (CRC) or research assistants. The randomization sequence table will be kept in the opaque sealed envelope by the CRO and should be opened according to Standard Operating Procedures (SOPs).

### Blinding

During the trial, clinical trial staff (investigator, CRC, research assistants) and the participant will be blinded to the type of drugs, which are randomly assigned by the web-based randomization system. In an emergency medical situation, such as, a serious adverse event (AE), unblinding will proceed according to the pre-defined plans by the CRO.

### Sample size calculation

Sample size will be not calculated because of the lack of research on the use of OJS in the treatment of patients with CHHF and pilot clinical trial for OJS. Considering visit frequency of CHHF patients and availability of workforce at each site, a total of 60 participants, 30 per group will be included.

### Participants

This study will enroll 60 patients with a complaint of CHHF, who meet the criteria shown in Table 2.

**Table 2 Tab2:** Eligible criteria

Inclusion criteria	
1. Female participants aged 19 to 59 years who complain of cold hypersensitivity in the hands and feet (CHHF) 2. Patients must have at least one of the following symptoms: (a) Symptoms of CHHF at a temperature at which most individuals feel no cold (b) Symptoms of extremely cold hands and feet upon exposure to cold (c) Continuance of symptoms of cold hands upon return to a warmer environment 3. Those with a CHHF Visual Analog Scale (VAS) score of 4 or higher 4. Those for whom the temperature of the palm (PC8) is lower than that of the upper arm (LU4) by 0.3 °C or more 5. Those who can comply with all study-related procedures, medications, and evaluations 6. Those who have completed a written informed consent form	
Exclusion criteria	
1. Those taking calcium antagonists or beta-blockers for the purpose of treating CHHF 2. Those with one or more ulcers or gangrene of the finger 3. Those who have been diagnosed with hypothyroidism or are taking thyroid-related medication 4. Those who are diagnosed with an autoimmune disease 5. Those who are diagnosed with carpal tunnel syndrome or have a positive result in Tinel and Phalen’s tests 6. Those who have been diagnosed with cervical disk herniation 7. Those who have been diagnosed with diabetes 8. Those who are currently medicated with drugs that may affect CHHF symptoms, such as anticoagulants 9. Those who have serious liver dysfunction (AST and ALT, each 100 IU/L or more) or renal dysfunction (creatinine (Cr) 2.0 mg/dL or more) 10. Those who do not (cannot) comply with treatment and follow-up due to mental illness such as behavior disorder, depression, anxiety neurosis, schizophrenia, or serious mental illness 11. Those who are diagnosed with moderate anemia and hematologic disorders (adult non-pregnant women hemoglobin (Hb) level less than 7 g/dL, hematocrit (Hct) level less than 26%, white blood cell (WBC) level 11,000/mm^3^ or more) 12. Those with systolic blood pressure (SBP) 180 mmHg or diastolic blood pressure (DBP) greater than 100 mmHg based on average value of at least 2 measurements 13. Those who have suspected arrhythmia requiring treatment on EKG, or have been diagnosed with heart diseases, such as, ischemic heart disease and so on 14. Those who are addicted to alcohol or drugs 15. Fertile women who are pregnant (positive urine-HCG), have a pregnancy plan, or do not agree to the appropriate method of contraception 16, Those who have been diagnosed with a malignant tumor 17. Those who are currently participating in other clinical trials 18. Those who are unable to understand and speak Korean 19. Those who are judged to be inappropriate for the clinical study by the researchers	

### Withdrawals

Voluntary participation and informed consent is mandatory for this trial before enrollment. All participants have the right to discontinue the study at any time. The detailed withdrawal criteria in this trial are as follows: occurrence of a serious AE either due to IP or other reasons; detection of a systemic disease that was not discovered at the screening stage; less than 70% compliance; subject’s withdrawal of consent; use of any forbidden medication or treatments (anticoagulants, psychotropic drugs, antidepressants, antithyroid medications, red ginseng, and other medications or treatments that may affect CHHF) during the trial that could affect the study result; subject who cannot be followed up. Reasons for withdrawal will be documented in case report forms (CRF) and data will be analyzed using the intention-to-treat (ITT) principle. For ensuring the retention of participants, each site research coordinator will responsible for making next visit-reminder phone calls.

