##### Cold stress test

The cold stress test (CST) is generally used to assess the severity of cold sensitivity in patients with vascular disorders [18]. For performing the procedure, the participants will rest for 20 min in the examination room (24 ± 1 °C) and then immerse both hands into a container of iced water (20 °C) for 30 s. The BTs of both palms (PC8) are assessed by using an infrared thermometer (Testo 835-T1, Lenzkirch, Germany), pre and post immersion and 6 min post immersion. The CST will be performed at visits 2 and 5. The recovery rate (RR) equation of the CST is as follows:$$ RR=\left({T}_6-{T}_0\right)/\left({T}_{\mathrm{base}}-{T}_0\right)\times 100\%, $$

where: *T*_base_: the skin temperature of PC8 at pre immersion

*T*_0_: the skin temperature of PC8 measured at post immersion

*T*_6_: the skin temperature of PC8 measured at 6 min post immersion

The higher RR represents faster recovery to normal temperature. The mean change of RR from baseline will be calculated to evaluate the efficacy of OJS.

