##### Korean version of the WHO Quality of Life-BREF

The mean changes of the WHO Quality of Life abbreviated version (WHOQOL-BREF) score from baseline will be assessed the quality of life of patients with CHHF symptoms. The WHOQOL-BREF is an effective, cross-culturally comparable, quality of life questionnaire. It consists of 26 items with five domains: general quality of life (2), physical health (7), psychological health (6), social relationships (3), and environmental health (8). To estimate quality of life scores in the Korean population, the Korean version of WHOQOL-BREF by Min et al. [19], will be used and measured at visits 2 and 4. Raw scores in each domain will be converted into a 0–100 transformed score where a higher score indicates better quality of life.

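### Low compliance and forbidden-medication use are grounds for leaving the trial rather than only for stopping the drug, so ITT with LOCF may impute week-8 values that could have been observed

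*Protocol article*

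**What the plan says.** The Withdrawals section introduces its list with "The detailed withdrawal criteria in this trial are as follows". Among the items are "less than 70% compliance" and "use of any forbidden medication or treatments". The second is limited to use during the trial that could affect the study result. Both stand in the same list as withdrawn consent and loss to follow-up. The section ends: "Reasons for withdrawal will be documented in case report forms (CRF) and data will be analyzed using the intention-to-treat (ITT) principle".

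The Statistical analysis section makes ITT the main efficacy analysis, in all who took at least one dose. It fills missing data by LOCF and restricts PP to those who complete the trial.

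On timing, Trial design and setting says: "The participants will be asked to return any unused investigational drugs at every visit to monitor adherence in order to calculate compliance". Table 1 schedules the compliance check at visits 3 (D28) and 4 (D56), and VAS at every visit. The cold stress test appears at visit 2 and visit 4. The Cold stress test section says instead "The CST will be performed at visits 2 and 5", and sets the endpoint: "The mean change of RR from baseline will be calculated to evaluate the efficacy of OJS". The WHOQOL-BREF section says the questionnaire "will be used and measured at visits 2 and 4", whereas Table 1 also has it at visit 3 and follow-up.

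**The concern.** ITT is meant to use each patient's outcome whatever her adherence. Here, poor adherence or use of another treatment can itself end her participation, and LOCF then supplies a value in place of the one she could have given. Both events happen after randomization and may differ between arms, for example through tolerability or lack of effect. Withdrawn consent and loss to follow-up make later data hard or impossible to obtain. These two reasons do not, so the gap comes from the protocol's own rule. A statistical analysis plan cannot recover a visit that never took place. The stakes are some distortion of this pilot's estimates, and the rule passing unchanged into the larger trial the pilot is meant to inform.

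**Working it through.** The article states no withdrawal rate, effect size or SD, so there is no figure to reproduce. The check traces the rules and then illustrates size under assumptions.

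**Step 1: does withdrawal mean leaving the trial?** The Withdrawals section speaks of criteria in the trial, and does not separate stopping drug from leaving. The Adverse event (AE) reporting section sets withdrawing against continuing to participate in the trial. That is the more natural reading, although the article nowhere says that assessments cease.

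**Step 2: which value is carried?** The abstract's time point, week 8 (D56), is used.

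- Low compliance enforced at visit 3: the D28 VAS.
- Low compliance first found at visit 4: the D56 VAS exists, so nothing is imputed for it.
- Forbidden medication before D28: baseline VAS. Between D28 and D56: the D28 VAS.
- Recovery rate: one test after baseline under either visit label. If it is missed and baseline is carried, the change is baseline minus baseline = 0.
- WHOQOL-BREF: the same zero only if the text schedule (visits 2 and 4) is followed. Under Table 1 a visit 3 value exists.

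**Step 3: size.** From the article: 30 per arm. Assumed: mean VAS change -3 on OJS and -2 on placebo, which withdrawn patients would also have reached (true difference -1.0); share f of that change present at the carried visit, with f = 0.5 for D28 and f = 0 for baseline; recovery-rate changes of +20 and +10 points (true difference 10). With wO and wP the shares withdrawn on OJS and placebo:

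VAS estimate = -3 × [1 - wO(1 - f)] + 2 × [1 - wP(1 - f)]

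Recovery-rate estimate = 20(1 - wO) - 10(1 - wP)

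| Withdrawn, OJS/placebo | VAS, D28 carried | VAS, baseline carried | Recovery rate |
|---|---|---|---|
| 1/1 | -0.98 | -0.97 | 9.7 |
| 3/3 | -0.95 | -0.90 | 9.0 |
| 3/0 | -0.85 | -0.70 | 8.0 |
| 0/3 | -1.10 | -1.20 | 11.0 |
| 6/6 | -0.90 | -0.80 | 8.0 |
| 9/3 (stress case) | -0.65 | -0.30 | 5.0 |

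For example, 3/0 with D28 carried: -3 × 0.95 + 2 = -0.85. Per patient, D28 carried shifts the VAS difference by 1.5/30 = 0.05 toward zero for OJS and by 1.0/30 = 0.033 away from zero for placebo.

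**Step 4: against the noise.** SE = SD × √(2/30), which is 0.39, 0.52 and 0.65 for assumed SDs of 1.5, 2.0 and 2.5. In the first five rows the largest VAS shift is 0.30, below all three. In the stress row the shifts are 0.35 and 0.70. The second exceeds the SE, but needs nine OJS patients withdrawn before D28, ahead of the first scheduled compliance check.

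**Step 5: direction.** With no true difference (both arms -2, f = 0.5), 3/0 gives -2 × 0.95 + 2 = +0.10 and 0/3 gives -2 + 2 × 0.95 = -0.10. If withdrawn patients would have stayed at their D28 value, the bias is 0. If three OJS patients would have returned to baseline after D28, the true value is -3 × 0.90 + 2 = -0.70, and the LOCF figure of -0.85 overstates the effect.

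**The case against.** The strongest reply is that a condensed article lists reasons for withdrawal and leaves the procedure at withdrawal to the full protocol. If that document requires an early-termination assessment, the carried values may not arise. This stands as a condition on the point. It does not remove it, because the wording as published points to leaving the trial and provides for no later assessment.

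Other limits also stand. The article does not say when the 70% rule is applied; if it is applied only at visit 4, the compliance part falls away for the D56 VAS. The forbidden-medication rule covers only use that could affect the result, and the Interventions section asks patients to consult the investigator before taking other drugs, so the group may be small. The article also does not say whether LOCF carries a baseline value when nothing follows it. The one-dose ITT set makes that plausible but does not settle it. A reader might infer that every such patient is certain to be imputed and to get a recovery-rate change of exactly 0. The documents support only the conditional statement.

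Finally, keeping these patients under observation brings values under other treatment into the main analysis, which some would regard as a different question. That is a fair cost to name, but it fits the ITT principle the protocol has already chosen.

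**Conclusion.** The point holds in conditional form. As written, two adherence-related events are grounds for leaving the trial, and dosed patients who leave before D56 are imputed in the main analysis although they could probably still have been seen. For compliance this requires enforcement at visit 3; for both reasons it requires that no assessment is made at or after withdrawal. The zero recovery-rate change further requires baseline to be carried.

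Size and direction are unknown. Under the assumed inputs, the VAS shift for up to three withdrawals in one arm, or six in each, stays below the standard error, and it can go either way. A reader might infer that the primary result is materially biased, or always biased toward no effect. The documents give no rates or effects to support either. This is a modest improvement for a pilot with 50 of 60 patients already recruited (Trial status). Its greater value is for the full trial.

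**What to change.** Amend the Withdrawals section so that compliance below 70% and use of forbidden medication that could affect the result end study drug only. Keep the scheduled D28, D56 and D84 assessments, including the end-of-treatment cold stress test, unless consent is withdrawn, and use the observed values in ITT. Because these patients would then complete the trial, redefine PP as at least 70% compliance and no forbidden medication, so that they remain outside it.

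The cost is a short amendment with IRB approval and staff training at three sites, as the ethics section requires, and no new visits or procedures. Off-treatment values, or values under other treatment, would enter ITT. The change reaches only the last 10 recruits and patients still in follow-up, so follow-up rules would differ within the trial. The same wording should go into the later full trial from the start.
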